## LIST OF ABBREVIATIONS

|           |                                        |        |                                     |
|-----------|----------------------------------------|--------|-------------------------------------|
| AE:       | Adverse event                          | SC:    | Steering Committee                  |
| ADR:      | Adverse drug reaction                  | SOFA:: | Sequential Organ Failure Assessment |
| AIFA:     | Italian medicines agency               | UFH:   | Unfractionated Heparin              |
| aPTT:     | Adjusted Partial Pro-thrombin time     | VFDs:  | Ventilation free days               |
| ALT:      | Alanine aminotransferase               | WHO:   | World Health Organization           |
| ARDS:     | Acute Respiratory distress syndrome    |        |                                     |
| AST:      | Aspartate aminotransferase             |        |                                     |
| BGA:      | blood gas analysis                     |        |                                     |
| CMV:      | cytomegalovirus                        |        |                                     |
| COVID-19: | Corona Virus 19 Disease                |        |                                     |
| CRP:      | C-reactive protein                     |        |                                     |
| DIC:      | Disseminated Intravascular coagulation |        |                                     |
| DSMB:     | Data Safety Monitoring Board           |        |                                     |
| EC:       | ethical committee                      |        |                                     |
| eCRF:     | electronic Case Report Form            |        |                                     |
| GCP:      | good clinical practice                 |        |                                     |
| H:        | hours                                  |        |                                     |
| Hb:       | Haemoglobin                            |        |                                     |
| HCT:      | Hematocrit                             |        |                                     |
| HFDs:     | Hospital free days                     |        |                                     |
| IFDs:     | Intensive Care Unit free days          |        |                                     |
| IL-6      | Interleukin-6                          |        |                                     |
| HR:       | Hearth rate                            |        |                                     |
| ICU:      | Intensive Care Unit                    |        |                                     |
| INR:      | International normalised ratio         |        |                                     |
| LMWH:     | Low Molecular Weight Heparin           |        |                                     |
| MAP:      | Mean arterial pressure                 |        |                                     |
| MRC:      | Medical Research Council               |        |                                     |
| n-CoV:    | New Corona Virus                       |        |                                     |
| PCT:      | Procalcitonin                          |        |                                     |
| PI:       | principal investigator                 |        |                                     |
| PLT:      | platelets                              |        |                                     |
| PT:       | pro-thrombin time                      |        |                                     |
| RR:       | Respiratory rate                       |        |                                     |
| SAPS II:  | Simplified Acute Physiology Score II   |        |                                     |

## **1.0 INTRODUCTION**

### **1.1 BACKGROUND AND RATIONALE**

In December 2019, a cluster of acute respiratory illness caused by SARS-CoV-2 virus occurred in Wuhan, Hubei Province, China. The disease has rapidly spread from Wuhan to many other countries worldwide, rapidly becoming a global health emergency.

Although most patients have mild manifestations and good prognosis after infection, some patients develop severe symptoms and die from multiple organ complications. Pneumonia is the most frequent and serious complication of COVID-19, the disease that results from SARS-CoV-2 infection.

The pathogenesis of SARS-CoV-2 infection in humans remains unclear, although it is very likely that the most severe manifestations of COVID-19 may be linked to host-pathogen interaction immune mechanisms.

SARS-CoV-2 infection seems to induce in most critical cases an excessive and aberrant hyper-inflammatory host immune response that is associated with a so-called "cytokine storm", characterized by plasma increase of infection-related biomarkers and of many cytokines and chemokines documented in many observational studies. These immunological derangements result in acute respiratory distress syndrome, characterized by typical radiological findings and that produce long-term damages such as fibrosis of lung tissue and organ harms. Moreover, during hospitalization, most patients were shown to have other immunological disorders such as marked lymphopenia, which was more pronounced over time among non survivors and specific depletion of regulatory T-lymphocytes.

This hyper-inflammatory immune response model is frequently observed in most severe forms of community acquired pneumonia and ARDS, where the detection of a strong systemic cytokine response (quantified with interleukin-6 and -10) is linked to poor therapeutic response and greater mortality.

Pro-thrombotic derangements of haemostatic system is another common finding in most severe forms of COVID-19 infections, which may be explained by the activation of coagulative cascade primed by inflammatory stimuli, in line with what is observed in many other forms of sepsis. As a matter of fact, D-dimer elevation and CID-score alteration are common finding in this patients and seems to correlate with patients' outcome.

Currently, while many antiviral and immune-modulatory drugs are under investigation, there is no proven specific antiviral drug against SARS-CoV-2 virus, the only treatment consist in support therapies such as mechanical ventilation. Targeting inflammatory responses along with thrombosis prevention may be a promising therapeutic option to improve patients' outcome.

#### **1.1.2 Benefits on the use of steroids**

Studies on community-acquired pneumonia show that the excessive production of locally pulmonary cytokines induced by pulmonary infection may cause a severe host inflammatory response inducing pulmonary dysfunction, increasing ICU admission and mortality. Steroids exert potent anti-inflammatory activity by inhibition of leucocytes extravasation, function of macrophages and antigen-presenting cells, production of TNF-alpha, interleukin-1 and nitric oxide. A Chinese report on 201 patients with COVID-19 pneumonia pointed out a survival benefit of more than 15% among patients with ARDS who received Methylprednisolone compared to those who did not.

An interesting report on post-mortem pathological findings in a SARS-CoV-19 patient with ARDS found out interstitial mononuclear inflammatory infiltrates dominated by lymphocytes, in both lungs, implying a severe

immune injury, pulmonary oedema and hyaline membrane formation, finding that suggest a possible role of steroids in this disease' treatment.

Nonetheless, corticosteroid treatment is a double-edged sword and their use remains controversial.

World Health Organization (WHO) recommend against the systematic use of corticosteroids for treatment of viral pneumonia. This recommendation is mainly driven by retrospective observational studies led on SARS, MERS and influenza virus showing no survival benefit and a decelerated viral clearance without affecting the outcome together with the consideration of the many steroid-related possible harms such as secondary infections, gastro-intestinal bleeding and long-terms side-effects.

On the other hand, WHO itself through the Blueprint process has prioritized studies on steroids as an additional therapy that can improve patients' outcome in order to identify actions that can save lives in the immediate aftermath of the COVID-19 pandemic.

Because of methodological limitations in the available evidence, some scientific societies such as Chinese Thoracic Society have developed an expert consensus statement sustaining the use of corticosteroids in 2019-nCoV pneumonia.

### **1.1.3 Benefits on the use of unfractionated heparin**

Several studies have demonstrated the tight interconnection between thrombosis and inflammation, two processes mutually reinforcing. Both coagulation factors and platelets are directly implicated in the modulation of the host immune response, displaying pro-inflammatory functions independent of their haemostatic effects.

Very recently, a severe derangement in coagulation parameters, showing a pro-thrombotic tendency, has been associated to a poor prognosis in patients affected by COVID-19. Moreover, in the same patients' cohort, the use of Low Molecular Weight Heparin (LMWH) or Unfractionated Heparin (UFH) at prophylactic doses has been demonstrated to be associated with a reduced 28-day in more severe patients with Sepsis Induced Coagulopathy (SIC) score  $\geq 4$  (40.0% vs 64.2%,  $P=0.029$ ), or D-dimer  $> 6$  fold of upper limit of normal (32.8% vs 52.4%,  $P=0.017$ ).

This finding agrees with the already described immune-modulatory properties and protective action of glycocalyx from shedding displayed by heparin.

Despite the biological plausibility, no good evidence is available on the efficacy and safety of heparin on sepsis patients, and many issues have to be addressed, regarding the proper timing, dosages and administration schedules of anticoagulant drugs.

## **1.2 STUDY OBJECTIVE**

The primary objective is to assess the hypothesis that an adjunctive therapy with steroids and unfractionated heparin or with steroids and molecular weight heparin (LMWH) are more effective in reducing any-cause mortality in critically-ill patients with pneumonia from COVID-19 infection compared to low molecular weight heparin (LMWH) alone. Mortality will be measured at 28 days.

A possible result showing the efficacy of the composite treatment in reducing the mortality rate among critically ill patients with pneumonia from COVID-19 infection will lead to a revision of the current clinical approach to this disease.

### **1.3 TRIAL DESIGN**

The study is designed as a multicenter, national, interventional, randomized, investigator sponsored, three arms study. Patients, who satisfy all inclusion criteria and no exclusion criteria, will be randomly assigned to one of the three treatment groups in a ratio 1:1:1.

## **2.0 METHODS: PARTICIPANTS, INTERVENTIONS AND OUTCOMES**

### **2.1 STUDY SETTING**

The study will involve 8 Italian Academic and non-Academic Intensive Care Units.

See list of centres in APPENDIX 1.

### **2.2 ELIGIBILITY CRITERIA**

#### **2.2.1 Inclusion Criteria**

1. Positive SARS-CoV-2 diagnostic (on pharyngeal swab of deep airways material)
2. Positive pressure ventilation (either non-invasive or invasive) from > 24 hours
3. Invasive mechanical ventilation from < 96 hours
4. P/F ratio  $\leq 150$
5. D-dimer level  $\geq 6$  x upper limit of local reference range
6. PCR  $\geq 6$  fold\_upper limit of local reference range

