### **2.4.2 Secondary Endpoints:**

- Ventilation free days (VFDs) at day 28, defined as the total number of days that patient is alive and free of ventilation between randomisation and day 28 (censored at hospital discharge). Ventilation is considered as positive pressure ventilation, either invasive or non-invasive. Periods of assisted breathing lasting less than 24 hours for surgical procedures will not count against the ventilation free days calculation;
- Need of rescue administration of high-dose steroids or immune-modulatory drugs;
- Occurrence of switch from non-invasive to invasive mechanical ventilation during ICU-stay;
- Delay from start of non-invasive ventilation to switch to invasive ventilation;
- All-cause mortality at ICU discharge and hospital discharge;
- ICU free days (IFDs) at day 28, defined as the total number of days between ICU discharge and day 28. If death occurs during the ICU stay before day 28 the ICU free days calculation will be 0. The ICU readmission before day 28 after randomization will be considered;
- Occurrence of new infections from randomization to day 28; including infections by Candida, Aspergillus, Adenovirus, Herpes Virus e Citomegalovirus
- Occurrence of new organ dysfunction and grade of dysfunction during ICU stay. Organ dysfunction is defined as a Sequential Organ Failure Assessment (SOFA) score  $\geq 3$  occurring after randomization, grade of dysfunction is measured with SOFA score (see SOFA score in APPENDIX 4) daily from randomization to ICU discharge (censored at day 28);
- Objectively confirmed venous thromboembolism, stroke or myocardial infarction;
- Occurrence of major bleeding (safety end point), defined as transfusion of 2 or more units of packed red blood cells in a day, bleeding that occurs in at least one of the following critical sites [intracranial, intraspinal, intraocular (within the corpus of the eye; thus, a conjunctival bleed is not an intraocular bleed), pericardial, intra-articular, intramuscular with compartment syndrome, or retroperitoneal], bleeding that necessitates surgical intervention and bleeding that is fatal (defined as a bleeding event that was the primary cause of death or contributed directly to death);

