### **3.0 METHODS: ASSIGNEMENT OF INTERVENTIONS**

#### **3.1 Allocation and blinding**

A block randomisation will be used with variable block sizes (block size 4-6-8), stratified by 3 factors: Centre, BMI (<30; ≥30) and Age (<75 e ≥75). Central randomisation will be performed using a secure, web-based, randomisation system. The allocation sequence will be generated by the study statistician using computer generated random numbers. The attending physician, according to the protocol and the randomization, will note the inclusion of the patient in the study. Clinicians will receive all the instructions to attend the protocol and paper printed instructions will be distributed in the participating centres. The local coordinator will be responsible of the training and information of the personnel about the study protocol. The study is conceived as open-label: the patients and all the healthcare personnel will be aware of the group allocation.

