- Routine laboratory test parameters for organ function assessment: haemoglobin, platelets count, white blood cells count, troponin, coagulative parameters (INR, PT, aPTT), parameters for liver (AST, ALT, bilirubin) and renal function (creatinine) will be recorded daily from inclusion to day 7 and then at day 14, 21, 28, censored at ICU discharge;
- Blood cells count, C-reactive protein (CRP) and procalcitonin (PCT), IL-6, immunoglobulins titers (IgG, IgA, IgM) will be recorded daily from inclusion to day 7 and then at day 14, 21 and 28, censored at ICU discharge;
- Beta-D Glucan in the blood and/or Galactomannan in the BAL will be recorded at admission and then every 3-5 days, censored at ICU discharge
- Ventilation mode (spontaneous breathing or mechanical ventilation), inspired oxygen fraction and arterial blood gas analysis parameters will be recorded daily from inclusion to ICU discharge, censored at day 28;
  - Adjunctive treatment such as pronation cycles, Nitric Oxide or ECMO will be recorded daily from inclusion to ICU discharge from (censored at day 28);
- New blood, respiratory and urinary-tract infections and the implicated microorganisms will be recorded from randomization to day 28;
- Viral reactivation measured by ADENOVIRUS, HSV e CMV DNA titres will be recorded from randomization to day 28, censored at ICU discharge;
- Need of renal replacement therapy: from randomization to 28 days, censored at ICU discharge.

D) Primary Outcome:

- All-cause mortality will be measured at day 28.

E) Secondary Outcomes:

- All-cause mortality will be measured at ICU discharge and hospital discharge
- SOFA score and its components will be recorded daily from randomization to ICU discharge (censored at day 28);
- Ventilation free days (VFDs) at day 28, measured at day 28;
- ICU free days (IFDs) at day 28, measured at day 28;
- Need of rescue administration of high-dose steroids or immune-modulatory drugs, measured from randomization to ICU discharge, censored at day 28;
- Switch from non-invasive to invasive mechanical ventilation from randomization to ICU discharge, censored at day 28;
- Occurrence of new infections will be recorded from randomization to day 28;
- Occurrence of objectively confirmed venous thromboembolism, stroke or myocardial infarction will be recorded from randomization to day 28;
- Occurrence of protocol related adverse events (see chapter 5.2) at day 28 (safety endpoint).

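### Inclusion criterion 3, as worded, makes invasive ventilation mandatory at entry, which conflicts with the switch endpoint counted from randomisation and leaves the delay endpoint uninformative

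*Protocol*

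**What the plan says.** Protocol Section 1.3 sets the entry rule: "Patients, who satisfy all inclusion criteria and no exclusion criteria, will be randomly assigned". Section 2.3 repeats it.

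Two of the six inclusion criteria in Section 2.2.1 concern ventilation:
- Criterion 2: "Positive pressure ventilation (either non-invasive or invasive) from > 24 hours".
- Criterion 3: "Invasive mechanical ventilation from < 96 hours".

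Two secondary endpoints in Section 2.4.2 concern the move to invasive support:
- "Occurrence of switch from non-invasive to invasive mechanical ventilation during ICU-stay".
- "Delay from start of non-invasive ventilation to switch to invasive ventilation".

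Appendix 4, note E, fixes the window of the first of these: "Switch from non-invasive to invasive mechanical ventilation from randomization to ICU discharge, censored at day 28". The delay endpoint does not appear in that note's list of secondary outcomes.

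**The concern.** Criterion 3 stands as its own item and has no conditional word to confine it to patients who are already intubated. Because every criterion must be met, a patient on non-invasive support alone fails it. A switch endpoint counted from randomisation makes sense only if such patients are randomised, so the eligibility text and the endpoint list describe different populations.

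Two things are at stake. The first is who gets in: Section 2.1 names 8 centres, and a centre that applies the criterion as written and one that treats it as an upper limit could enrol different patients. The second is whether the two endpoints measure anything that treatment can change. An analysis plan can refine an analysis set, but it cannot settle who is eligible.

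**Working it through.** This is mainly a check of consistency, so the texts are set side by side under each reading of criterion 3.

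**Can criteria 2 and 3 hold together?** Yes. Criterion 2 sets a minimum (more than 24 h) for total positive pressure ventilation. Criterion 3 sets a maximum (less than 96 h) for invasive ventilation. A patient with 30 h of non-invasive and then 2 h of invasive ventilation meets both, and so does one with 48 h of invasive ventilation. A patient with 30 h of non-invasive ventilation and no intubation meets criterion 2 and, read literally, fails criterion 3.

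**The two readings against the two endpoints**

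| | Criterion 3 mandatory (literal) | Criterion 3 an upper limit for intubated patients |
|---|---|---|
| Non-invasive support only at entry | Excluded | Eligible |
| Switch, from randomisation | No patient at risk of a first switch; only extubation to non-invasive support and then re-intubation could count | Valid randomised comparison among patients on non-invasive support at randomisation |
| Delay from start of non-invasive support to switch | For the initial intubation, complete before randomisation: a baseline quantity | Open to treatment only in patients who switch after randomisation: a comparison of subgroups selected after randomisation |

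In the last cell, a treatment that prevents intubation also changes who contributes a delay. A difference in mean delay between arms could therefore reflect who switched rather than how long switching was postponed.

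**Does the sample size depend on this?** Inputs from Section 2.6: control mortality 50%, absolute reduction 25 points (so 25% on treatment), two-sided alpha 2.5%, power 80%, allocation 1:1:1.

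n per arm = [z(0.9875)·√(2·p̄·(1−p̄)) + z(0.80)·√(p₁(1−p₁) + p₂(1−p₂))]² / (p₁−p₂)²

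With p̄ = 0.375: [2.2414·√0.46875 + 0.8416·√0.4375]² / 0.0625 = (1.5346 + 0.5567)² / 0.0625 = 69.97, rounded up to 70. Three arms give 210, as stated. No ventilation input enters the formula.

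**Illustration for the upper-limit reading.** The protocol gives neither the share of patients on non-invasive support at entry nor any switch rate. Assume switch risks of 50% and 25%, purely for illustration, at alpha 2.5%, with 70 per arm multiplied by the share:

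power = Φ{[0.25·√n − 2.2414·√0.46875] / √0.4375}

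| Assumed share on non-invasive support | n per arm | Power |
|---|---|---|
| 10% | 7 | 9% |
| 25% | 17.5 | 23% |
| 50% | 35 | 47% |

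Even with a large assumed effect, the switch endpoint would be supportive information only at these shares.

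**The case against.** Several stronger readings are tempting, and the protocol does not support them.

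- **That criteria 2 and 3 contradict each other.** They do not; both can be true of one patient. Even on the literal reading, the mention of non-invasive support in criterion 2 has a use, because non-invasive hours before intubation count towards the 24 h. The conflict is between Section 2.2.1 and the endpoints in Section 2.4.2 and Appendix 4.
- **That the switch endpoint is impossible.** Section 2.4.2 does not limit it to the first intubation, so re-intubation after a return to non-invasive support could count. The endpoint loses its evident purpose but need not be zero.
- **That the switch endpoint has the wrong denominator and is diluted.** The protocol fixes no denominator. Section 4.2.1 names the relative risk for binary outcomes, and adding patients not at risk in equal proportion leaves it unchanged: with an assumed 30% at risk, (0.30 × 25%) / (0.30 × 50%) = 7.5% / 15% = 0.50, the same as 25% / 50%. Only the absolute difference shrinks. At-risk sets and the handling of death as a competing event commonly belong in an analysis plan, which is not at hand.
- **That both endpoints are non-randomised comparisons.** This applies to the delay only. A clock that starts before randomisation is not in itself a bias; the problem is restriction to those who switch.
- **That the trial's mortality assumption fails.** Section 2.6 ties the 50% to ICU patients generally and to neither reading. Different case mix between centres is possible but not shown, and stratification by centre (Section 3.1) means that differing local readings would not be expected to unbalance the arms.

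All five limits stand. They leave the core untouched: no text available for this check says that criterion 3 is only an upper limit. The flow-chart in Appendix 2 could not be read.

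**Conclusion.** The point holds as an internal inconsistency. Criterion 3 together with the all-criteria rule excludes patients on non-invasive support only, while a listed secondary endpoint with a window starting at randomisation presupposes them. On the literal reading no patient is at risk of a first switch. The delay endpoint is unsatisfactory on either reading, for a different reason each time, and its absence from Appendix 4 is a further mismatch.

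The consequence is an eligibility rule open to two readings and two secondary endpoints that cannot be interpreted as they stand. The definition of 28-day mortality and the sample size of 210 are unaffected. The conclusion rests on wording alone; the power figures are illustrations under assumed shares and switch rates and carry no weight in it.

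**What to change.** Reconcile Sections 2.2.1 and 2.4.2 and Appendix 4 by stating whether criterion 3 is a condition that every patient must meet or only a time limit for patients already on invasive ventilation. That choice is the sponsor's.

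- **If mandatory:** delete the switch and delay endpoints from Section 2.4.2, and the switch from Appendix 4.
- **If an upper limit:** reword criterion 3 so that it applies only to patients who are invasively ventilated. Analyse the switch among patients on non-invasive support at randomisation. Replace the delay among switchers by time from randomisation to intubation in that same group, and list it in Appendix 4.

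In the upper-limit case, also confirm that the daily ventilation-mode field separates non-invasive from invasive support. Appendix 4 glosses it with only two states, breathing spontaneously or being mechanically ventilated, which does not make that distinction explicit.

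The cost is a short protocol amendment, which Section 6.1 puts before the Ethics Committee, an adjusted eligibility check in the eCRF and, if the mode field proves too coarse, one extra category. No change to the sample size is needed.
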